#### Secondary outcome measures

Between group differences in the following:
Rate of radiologically verified recurrence at 3 years.Mean GSRS (gastrointestinal symptoms rating scale) component scores of reflux, abdominal pain, indigestion, diarrhea, and constipation at 3 months, 1 year, and 3 years postoperatively.Mean Short-Form 36 (SF-36) physical and mental component scores at 3 months, 1 year, and 3 years postoperatively.Mean Dakkak dysphagia scores at 3 months, 1 year, and 3 years postoperatively.Frequency of reflux disease-related symptoms (heartburn, reflux, chest pain, dysphagia of liquids and/or solids, odynophagia, globus sensation, respiratory symptoms, nightly cough, and odynophagia categorized on a four-level scale at 3 months, 1 year, and 3 years postoperatively).Rates and severity of complications at 30 days postoperatively. Complications will be classified according to Clavien-Dindo [34].Mean postoperative length of stay in days.Size and type of recurrence. Size will be measured in cm above the diaphragm. Type will be classified as types I–IV.

These metrics were chosen to assess both the objective and subjective effectiveness of the intervention as well as the safety. There is currently no core outcome set available that defines standardized outcome indicators for paraesophageal hernia repair, although it is in development [35]. The GSRS, SF-36, and Dakkak questionnaires are all validated instruments [36–38]. The reflux disease-related frequency questionnaire has been used in numerous previous studies from the same institution. Taken together, these instruments enable a comprehensive coverage of symptoms related to paraesophageal hernias.

### Participant timeline {13}

**Table Tabb:** 

	Enrolment	Allocation	Follow-up		Close-out
Timepoint	-t_1_	0	3 m	1 y	3 y
**Enrolment**					
Eligibility screen	X				
Informed consent	X				
Allocation		X			
**Interventions**					
Control		X			
Intervention		X			
**Assessments**					
QoL and symptom questionnaires	X		X	X	X
Computed tomography	X			X	X
Endoscopy	X				

### Sample size {14}

Previous studies have suggested recurrence rates after paraesophageal hernia repair ranging from 7 to 66% [15–20]. We have estimated the recurrence rate to be 30% in the control group and hypothesize that this can be reduced to 10% with the addition of gastropexy. With an α of 0.05 and a power of 80% (β = 0.2), we calculate a required sample size of 62 participants per arm, yielding a total of 124 evaluable participants. To account for an estimated 15% loss to follow-up, based upon previous studies with similar follow-up at the same institution, we aim to include 150 participants. The primary analysis will use multiple imputation under a missing-at-random assumption to include all randomized participants; this approach is expected to preserve the planned power under the anticipated missingness.$$\begin{aligned}n&=\left[\sqrt{\frac{\left(0.3+0.1\right)}{2}\left(1-\frac{\left(0.3+0.1\right)}{2}\right)\left(1+\frac{1}{1}\right)}\ 1.96\ \right.\\&\left.+\ \sqrt{0.3\left(1-0.3\right)+\frac{0.1\left(1-0.1\right)}{1}}0.84\right]^{2}/{0.2}^{2}\approx 62\end{aligned}$$

### Recruitment {15}

This multicenter trial currently includes six centers, with additional centers being invited to participate. The annual volume of PEH repairs varies across the centers, but the majority perform more than 20 cases annually. Based on these volumes, we anticipate reaching our target of 150 participants included within the projected recruitment period of 2–3 years.

## Assignment of interventions: allocation

### Sequence generation {16a}

Participants will be assigned to either the control or intervention group with a 1:1 allocation ratio. A computer-generated randomization list in blocks of 10 for high-volume centers and six for low-volume centers will be used. Stratification will be performed by center only.

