### Concealment mechanism {16b}

Allocation will be concealed using sealed, opaque, sequentially numbered envelopes. The envelopes will be opened in the operating theatre after induction of anesthesia, immediately prior to commencement of the procedure.

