### Implementation {16c}

The randomization sequence will be generated centrally by the central study coordinator prior to trial initiation. Sealed envelopes will be prepared, shuffled independently by research nurses, and distributed to the participating sites. Participants will be enrolled locally by the treating surgeon or research nurse.

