## Assignment of interventions: blinding

### Who will be blinded {17a}

The outcome assessors and participants will be blinded during the entire follow-up ending at 3 years after the surgical PEH repair. The operation report, with information on the specific type of repair performed, will not be included in the digital patient chart. Instead, a hard copy with information about the study group allocation will be kept in a sealed envelope, which is filed in a locked archive.

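### One fixed, published block length per centre lets anyone with a full tally of a centre's allocations know up to 25% (blocks of 6) or 17% (blocks of 10) of next allocations for certain

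*Protocol article*

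**What the plan says.** Sequence generation {16a} of the protocol article sets the scheme, under which a list generated by computer "in blocks of 10 for high-volume centers and six for low-volume centers will be used". The ratio is 1:1, and "Stratification will be performed by center only". Each centre therefore runs its own sequence with one block length, and no random variation of that length is mentioned.

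Concealment mechanism {16b} relies on envelopes: "Allocation will be concealed using sealed, opaque, sequentially numbered envelopes". As to timing, "The envelopes will be opened in the operating theatre after induction of anesthesia, immediately prior to commencement of the procedure".

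Under Implementation {16c}, the central study coordinator generates the sequence, and research nurses shuffle the envelopes before they go to the sites. The section does not say whether the shuffling stays within blocks. It adds: "Participants will be enrolled locally by the treating surgeon or research nurse".

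On blinding, section {17a} states: "The outcome assessors and participants will be blinded during the entire follow-up ending at 3 years after the surgical PEH repair". The operating team is not listed. The same section keeps the operation report out of the electronic chart and files the allocation in a sealed envelope in a locked archive.

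Trial status says that recruitment began on 27 June 2023 and should end by the close of 2026, so the block lengths are public while patients are still being randomised.

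**The concern.** With a constant, known block length, allocations become forced once one arm's places in the block are used up. The last allocation of every complete block is always determined, and often one or more before it. Operating staff learn allocations as they occur, and a treating surgeon may also be the person who enrols.

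An opaque envelope hides the next card but not this arithmetic. Opening it after induction prevents a reaction to a revealed allocation, but not anticipation of it. Because the envelope is tied to the operation, someone who knows the next card could influence which patient meets it, mainly through the order of the operating list. Blinded CT reading comes too late to undo such selection. What is at stake is comparability of the arms in a trial of 150 patients with a recurrence endpoint that depends on patient and hernia characteristics.

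**Working it through.** The protocol gives no figure for predictability, so there is none of its own to reproduce.

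**Inputs.** From Sequence generation {16a}: block length b = 6 or 10, 1:1 ratio, stratified by centre; write m = b/2 for the places per arm. From Sample size {14} and Recruitment {15}: 150 participants and six centres. Assumed: an observer who knows b and all earlier allocations at the centre, with envelopes issued in list order.

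**Share known for certain, complete blocks.** Forced allocations are those left after one arm is exhausted, that is, the run of identical allocations ending the block. In a random ordering of m and m, the expected length of that run is 2m/(m+1). Dividing by b = 2m gives a share of 1/(m+1).
- b = 6: 6/4 = 1.5 allocations per block; 1/4 = 25.0%.
- b = 10: 10/6 = 1.67 allocations per block; 1/6 = 16.7%.

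**Incomplete last block.** With equal recruitment, 150/6 = 25 patients per centre. For b = 10 there are two full blocks and five further patients, none of whose allocations can be forced: 2 × 1.667/25 = 13.3%. For b = 6 there are four full blocks and one further patient: 4 × 1.5/25 = 24.0%.

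**Share guessed correctly by naming the arm that is behind.** The expected number correct per block is m + (4^m/C(2m,m) − 1)/2.
- b = 6: 3 + (64/20 − 1)/2 = 4.10, or 68.3%.
- b = 10: 5 + (1024/252 − 1)/2 = 6.53, or 65.3%.

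This rule needs no block length. Every completed block is balanced, so the centre's running difference between arms equals the difference inside the current block. Chance is 50%.

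**Effect of varying the block size.** This was simulated with 30 patients per centre and equally likely sizes. The guesser knows the set of sizes, but not which one is in use, and always makes the best guess.

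| Scheme | Known for certain | Best guess correct |
|---|---|---|
| Fixed 6 | 25.0% | 68.3% |
| Fixed 10 | 16.7% | 65.3% |
| Random 4, 6, 8 | about 2.5% | about 67.6% |
| Random 6, 8, 10 | about 1.9% | about 65.7% |

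The fixed rows are the exact values above. Varying the size removes nearly all certain knowledge and leaves the guess rate about where it was. At centres now using 10, a mix containing 4 moves the guess rate from 65.3% to about 67.6%; 6, 8 and 10 leave it at about 65.7%.

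**The case against.** The best case for the plan has five parts.

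- **Timing.** Allocation follows operating order, not consent order. A reader might infer that allocation can be predicted when a patient is invited. The documents do not support that: the surgeon would also need to know how many consented patients will be operated on first. This objection stands, and it moves the concern to scheduling and the hours before surgery.
- **Knowledge of past allocations.** Nothing says that one surgeon sees every case at a centre. Operation reports are kept out of the chart, and a research nurse may enrol instead. This stands as a reason to call the percentages upper bounds. It does not remove the concern, since surgeons at a centre with few operators can keep a tally.
- **The guess rate.** A reader might blame the fixed block length for the 65–68% of correct guesses. That is wrong: a tally alone gives this rate, and random block sizes leave it almost unchanged. Only the certain share depends on the fixed length.
- **Shuffling.** If nurses shuffled across blocks, the certainty figures do not apply. But then the envelopes no longer follow the blocked list in Sequence generation {16a}, so the two sections conflict. If they shuffled within blocks, the figures stand. Neither reading makes shuffling a stated remedy.
- **Adjustment.** The primary model includes age, BMI and hiatal area (Statistical methods {20a}), which bears directly on selection by hernia size. It does not cover tissue quality, frailty or other unrecorded judgement.

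**Conclusion.** The point holds in a limited form. The stated scheme makes up to 25.0% (blocks of 6) or 16.7% (blocks of 10) of next allocations certain to someone holding a centre's complete tally. At an average centre of 25 patients the shares are 24.0% and 13.3%. This rests on full knowledge of earlier allocations, envelopes in list order, and no shuffling across blocks; the 25-patient figures also assume equal recruitment. The opportunity lies chiefly at scheduling and just before surgery.

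A reader might go further and infer that selection has occurred. Nothing in the article shows that, and it is not claimed here. Nor is this a matter of detail left to a fuller document: the article itself states the block lengths. It is a cheap improvement to a rule that the plan fixes, and the sample size is unaffected.

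**What to change.** For all unissued envelopes and all newly joining centres:

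1. Generate each centre's list in permuted blocks whose sizes vary at random, for example 6, 8 and 10, and do not disclose the sizes to sites or in public text.
2. Number the envelopes in generated order and drop the shuffling step. State how the envelopes already issued were shuffled, so that the existing sequence can be described correctly.
3. Where possible, keep the list and the running tally away from those who enrol patients and set the operating order. This matters because varied sizes do not lower the best-guess rate.

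The expected gain is a fall in the share known for certain from 25.0% or 16.7% to about 2%. No gain in the guess rate should be claimed.

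The costs are a regenerated list, replacement of unused envelopes, and slightly more possible imbalance per centre at the end. A block left unfinished can put the arms out by at most half its length, so the limit rises from 3 to 5 at centres now using 6 and stays at 5 at those using 10. An old block cut short at the changeover can add up to 3 or 5 once. The benefit reaches only patients not yet randomised, a number that the article does not give.

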### Concealment mechanism {16b}

Allocation will be concealed using sealed, opaque, sequentially numbered envelopes. The envelopes will be opened in the operating theatre after induction of anesthesia, immediately prior to commencement of the procedure.

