**Methods:**

All patients scheduled for PEH repair are assessed for eligibility for enrolment. Preoperative work-up includes upper GI endoscopy, computed tomography, and symptom assessments. Participants will be randomized (1:1) to either the control or intervention group. In the control group, patients will have a standardized repair, including posterior crural repair and a total fundoplication. In the intervention group, a three-point gastropexy using running non-absorbable sutures will be added to the same reconstruction as in the control group: a posterior fixation of the wrap to the diaphragm, a lateral fixation of the left wrap to the diaphragm, and an anterior fixation of the minor curvature to the inner surface of the anterior abdominal wall. The primary outcome is computed tomography-verified radiological recurrence at 1 year. Secondary outcomes include radiological recurrence at 3 years, patient-reported quality of life, and disease-specific symptoms at 3 months, 1 year, and 3 years, as well as postoperative complications. The study design is double-blinded, with both participants and outcome assessors being blinded to the allocation of patients to treatment arms.

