### Intervention description {11a}

All surgeries will be performed under general anesthesia. The method used for abdominal entry, port placement, and type of liver retractor is at the surgeon’s discretion. Ultrasonic shears are used for dissection. The herniated viscera are completely reduced into the abdomen, and the hernia sac is fully dissected and resected. The esophagus is mobilized intraabdominally until at least 3 cm rests independently below the hiatus without tension. Effort is made to identify and preserve the anterior and posterior vagal nerves. A posterior crural closure with running non-absorbable sutures is performed. An additional anterior crural closure may be performed at the surgeon’s discretion. The fundus is mobilized to allow a floppy fundoplication. A total fundoplication is created by three interrupted non-absorbable sutures [31–33]. No bougies are used routinely for calibration of the fundoplication.

In the intervention group, in addition to the above, a three-point gastropexy is performed (Fig. 1). First, the right fundus flap is adapted posteriorly to the crural portion of the diaphragm with a 2–3 cm long running non-absorbable suture (“posterior gastropexy”). Second, the left fundus flap is adapted to the diaphragm anterolateral to the hiatus with a 2–3 cm long running non-absorbable suture (“left lateral gastropexy”). Finally, the minor curvature of the anterior stomach wall is adapted during reduced intraabdominal pressure to the anterior abdominal wall with a 2–3 cm long running non-absorbable suture (“anterior gastropexy”).

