### Criteria for discontinuing or modifying allocated interventions {11b}

If the surgeon deems it necessary to add adjunct procedures or deviate from the protocol in any other way, this is noted in the operative case report form as well as in the medical record.

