### Methods in analysis to handle protocol non-adherence and any statistical methods to handle missing data {20c}

With the randomization and intervention taking place in the operating room, we expect no protocol non-adherence. Prior to surgery, we will ensure that all preoperative questionnaires are completed, which should reduce the risk of missing baseline data. We will handle missing primary outcome data using multiple imputation by chained equations (MICE) under a missing-at-random assumption. The imputation model will include treatment group and pre-specified prognostic variables (including baseline characteristics and any available intermediate/follow-up measurements) to generate m imputed datasets; each dataset will be analyzed using the planned regression model for the dichotomous outcome (e.g., logistic regression), and estimates will be combined using Rubin’s rules.

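### The surgeon learns the allocation before the operation starts, so the discretionary parts of the shared repair are decided with knowledge of the arm

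*Protocol article*

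**What the plan says.** All references are to the protocol article.

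- **Timing.** Concealment mechanism {16b}: "The envelopes will be opened in the operating theatre after induction of anesthesia, immediately prior to commencement of the procedure".
- **Masked roles.** Section {17a} names two groups: "The outcome assessors and participants will be blinded during the entire follow-up ending at 3 years after the surgical PEH repair". The operating surgeon is not listed.
- **Difference between arms.** The abstract's Methods paragraph says that "a three-point gastropexy using running non-absorbable sutures will be added to the same reconstruction as in the control group". Intervention description {11a} sets out reduction, sac resection, esophageal mobilization, crural closure and fundoplication for everyone, and then states: "In the intervention group, in addition to the above, a three-point gastropexy is performed".
- **Room for judgement.** In {11a}, "An additional anterior crural closure may be performed at the surgeon’s discretion", and mobilization has a minimum of 3 cm but no upper limit. Section {11b} foresees departures, "If the surgeon deems it necessary to add adjunct procedures or deviate from the protocol in any other way", and has them noted in the operative case report form and the medical record.
- **Safeguards.** {11c} provides harmonization and review of site videos before the trial, with the gastropexy as the particular focus. {11d} requires the repair to follow the protocol strictly. {18a} has a blinded radiologist read the CT scans.

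**The concern.** The trial is meant to isolate the effect of adding gastropexy to an otherwise identical repair. That requires the repair itself to be the same, on average, in both arms. A surgeon who knows that no gastropexy will follow may compensate, for instance by adding an anterior closure or mobilizing further. A surgeon who believes in gastropexy may take more care when it is allocated. The protocol's Discussion accepts that many surgeons may prefer some fixation, so operator preference is a realistic influence.

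The Discussion also names lateral (crural) and axial (esophageal) tension as sources of strain on the repair, and the discretionary steps bear on both. If they differ by arm, their effect on recurrence is mixed with that of gastropexy. Randomisation does not balance what is decided after the envelope is opened. Compensation in the control arm would shrink the observed difference; extra care in the gastropexy arm would enlarge it.

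**Working it through.** **1. Order of events.** Setting {16b}, {17a} and {11a} side by side gives: induction; envelope opened; reduction, sac resection and mobilization; crural closure, with the anterior closure optional; fundoplication; then gastropexy if allocated. The surgeon knows the arm throughout the shared part. No section gives a reason for opening the envelope before it.

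**2. Which shared steps leave latitude.**

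| Shared step ({11a}, {11b}) | Specified to an endpoint? |
|---|---|
| Reduction of herniated viscera | Yes, complete |
| Sac dissection and resection | Yes, full |
| Mobilization | Minimum only (3 cm) |
| Posterior crural closure | Yes, in all patients |
| Anterior crural closure | No, surgeon's choice |
| Total fundoplication | Yes, three interrupted sutures |
| Adjuncts or deviations | No, if deemed necessary |

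The concern applies to the three rows without a fixed endpoint.

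**3. The plan's own figure.** Sample size {14} uses 30% v 10%, α 0.05 (two-sided, from the 1.96) and power 80%:

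n = [1.96·√(0.2·0.8·2) + 0.84·√(0.3·0.7 + 0.1·0.9)]² / 0.2² = 61.5, rounded up to 62 per arm.

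This reproduces. Allowing for 15% loss, 124/0.85 = 145.9, so 146, which the target of 150 covers.

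**4. Illustrations.** The bias sizes below are assumptions; none is in the documents. With n = 62 per arm, d = p1 − p2 and p̄ = (p1 + p2)/2:

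s0 = √(2·p̄(1 − p̄)/n), s1 = √([p1(1 − p1) + p2(1 − p2)]/n), c = 1.96·s0

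P(reject) = 1 − Φ((c − d)/s1) + Φ((−c − d)/s1)

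Planned case, 30% v 10%: s0 = 0.0718, s1 = 0.0696, c = 0.1408, (c − d)/s1 = −0.851, so P = 0.803.

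(a) Compensation lowers the control rate, gastropexy stays at 10%:

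| Control rate | Power |
|---|---|
| 30% (plan) | 80.3% |
| 27% | 68.8% |
| 25% | 59.6% |
| 20% | 34.3% |

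(b) No gastropexy effect, but arm-dependent conduct of the shared steps creates a gap:

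| Rates | Gap | P(significant) |
|---|---|---|
| 30% v 30% | 0 points | 5.0% |
| 30% v 27% | 3 points | 6.6% |
| 30% v 25% | 5 points | 9.5% |
| 22.5% v 17.5% | 5 points | 10.7% |
| 30% v 20% | 10 points | 24.9% |

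A 3- to 5-point gap therefore gives about 7% to 11% instead of 5%.

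**5. Do the safeguards reach this?** Harmonization and video review come before the trial and do not hide the arm in an individual case. The strict-adherence rule cannot constrain a step that the protocol leaves open: an arm-dependent anterior closure is fully adherent. Recording deviations makes them visible but does not prevent them. Blinded CT reading protects measurement, not the operation.

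**The case against.** The strongest reply is that the repair is standardized. Most shared steps have a fixed endpoint, techniques are harmonized and checked on video, and strict adherence is required. Opening after induction keeps the allocation concealed until the patient is anaesthetised. Deviations and adjuncts are already noted, so they can be compared by arm. Recruitment began on 2023-06-27 and is expected to end with 2026, so a change now covers only part of the sample and alters the point of randomisation mid-trial.

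Much of this stands. It narrows the concern to the discretionary steps and limits what an amendment can still achieve. It does not remove the point, because none of these measures hides the arm while those steps are decided, and later opening would keep both concealment and participant blinding.

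Three stronger readings are tempting, and the documents do not support them:

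- **Every shared step is biased.** The fixed endpoints in {11a} argue against this, and exposure to bias is not evidence of bias.
- **Hiatal area, a covariate in the primary model, is measured by someone who knows the arm.** Section {20a} does not say how it is measured, and every patient has a preoperative CT.
- **Early opening causes patients in both arms to receive the other arm's treatment.** A standard repair that proves impossible would not give a control patient a gastropexy, and no section supports a crossover rate. The statement in {20c}, "With the randomization and intervention taking place in the operating room, we expect no protocol non-adherence", does sit awkwardly with {11b}. That tension exists whenever the envelope is opened and adds no weight here.

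**Conclusion.** The point holds for the discretionary shared steps. The protocol fixes a time of opening that lets an unblinded surgeon decide on anterior closure, extra mobilization and adjuncts knowing the arm, and it gives no reason for doing so. The primary comparison is thereby exposed to performance bias in either direction.

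The size cannot be derived from the documents. The power and false-positive figures show only that modest shifts would matter with 62 evaluable patients per arm; no number in the protocol is wrong. They assume an unadjusted comparison of two proportions, whereas the planned analysis is covariate-adjusted logistic regression. The conclusion also assumes that operations follow the order in which {11a} describes them.

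This is an avoidable weakness that is cheap to reduce. It is not a fatal flaw.

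**What to change.** 1. For remaining patients, amend {16b} so that the envelope is opened only after crural closure and fundoplication are complete and any anterior closure or adjunct has been decided and recorded on the operative case report form, immediately before the point where gastropexy would be done.
2. Record the date of the change and the timing regime for each patient.
3. Log consented patients who are not randomised because of operative findings.
4. Report anterior closures, adjuncts and deviations by arm for all patients, including those already operated on. For the latter, this is the only available check.

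The cost is a short amendment and a theatre instruction, with no extra staff or procedure. The trial would then have two timing regimes. A few consented patients would never be randomised, so the randomised population may shift slightly after the change; items 2 and 3 make that visible. If the steering committee keeps the present timing, it should state why the arm must be known earlier and still carry out item 4.
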